### 2.2. Phase II: The Pilot Study and the Qualitative Process Evaluation

Study design of the pilot study

In phase II, the newly developed intervention protocol’s feasibility and acceptability will be tested using a pre-post pilot study incorporating a qualitative process evaluation.

(1)Pilot study: Study sample

The inclusion criteria will be female patients (1) aged 18 years or older; (2) confirmed diagnosis of breast cancer at stage I, II, or IIIa; (3) confirmed diagnosis of CVDs, such as heart failure, hypertension, coronary artery disease, cerebrovascular accidents (e.g., stroke, transient ischemic attack), cardiomyopathy and arrhythmias; (4) able to read, write, and communicate in English; (5) have completed active anticancer treatment including chemotherapy and radiotherapy, and are receiving regular healthcare in primary care centre from GP/practice nurses; (6) willing to participate in the research study and provide informed consent. The exclusion criteria: patients with unstable health conditions with mental health issues or critically ill patients unable to participate in physical activities (e.g., suffering from life-threatening diseases, extremely weak), cognitive impairment, currently involved in another research study, or scheduled anticancer treatment during the study period.

(2)Sample size and study settings

Based on the rule of thumb suggested by Julious [60], a sample size of 12 will be employed in this pilot single-group pre-post study. When taking into account a 20% dropout rate based on a clinical study by Cramer et al. [61], 15 participants will be recruited for this study.

(3)Study procedure

Potential participants will be identified and approached in collaboration with the primary care centres and the healthcare professionals. The participants will be informed of the study by the treating doctor or the centre by using flyers or through emails sent by the centre reception. The healthcare professionals at the centre will be introduced to the study through meetings, presentations or brochures to help with the recruitment and to distribute the participant information sheet. The interested participants will contact the primary researcher. Prior to recruitment, potential participants will be screened for eligibility, and informed consent will be obtained from eligible participants after explaining the study’s purpose, procedures, and risks. Participants will be advised to continue receiving usual care from their medical centre during the study.

The planned data collection will be taking place at three points during the study: at the beginning of the study before the intervention (T1). At week four immediately after the NGPS intervention (T2) and at week 12, which is eight weeks post-intervention (T3). The eight-week follow-up is based on previous research suggesting that it typically takes around eight weeks for individuals to change a habit or behaviour [62]. The interventions will be carried out through a combination of telehealth and in-person consultations, with alternating durations depending on the session type.

A qualitative process evaluation will be conducted at the end of the intervention, at week four by using semi-structured interviews. All the participants will be invited to participate in the qualitative interviews.

#### 2.2.1. Outcomes and Measurements

The study will employ a demographic data sheet that has been specifically developed by the research team to gather information on the socio-demographic characteristics of the patients, such as age, height, race/ethnicity, as well as their medical history, such as date of BC and CVD diagnosis, the current stage of BC, the type and date of BC and CVD treatment.

(1)Primary outcomes

The primary outcomes will be the feasibility, acceptability and safety outcomes. The feasibility outcome will measure the feasibility of the questionnaires, recruitment and the intervention delivery. The acceptability of the intervention will be assessed by assessing the acceptability among the participants. The safety of the intervention will be measured by the safe delivery of the intervention. The primary outcome will also measure the recruitment, retention, and dropout and will be evaluated as the fundamental aim.

The recruitment rate is the percentage of eligible participants who consented to participate in the study.The retention rate will measure the percentage of participants who remain in the study throughout the entire study period, from enrolment to follow-up (week 12).The dropout rate will be calculated based on the percentage of participants withdrawn from the study after enrolment.The feasibility of the questionnaires will be assessed by measuring the percentage of missing responses for each item and the entire scale.The feasibility of the recruitment will be assessed by measuring the number of weeks or months needed to achieve the target number of sample size.The adherence rate to the NGPS protocol will measure the percentage of participants who followed the interventions as intended. This will measure the feasibility and acceptability of the study intervention.The safety of the intervention includes discomfort or adverse effects related to NGPS intervention by keeping a daily logbook and reporting via telephone or face-to-face.Acceptability will assess the participant’s satisfaction, benefits received and obstacles faced using an investigator-created questionnaire.

(2)Secondary outcomes

The secondary outcomes will measure the physiological outcomes, which include weight, BMI, blood pressure and heart rate. The secondary outcomes will also evaluate the clinical outcomes, the preliminary effects of the NGPS intervention on various measures, behavioural outcomes, which include dietary outcomes, physical activity and smoking status; psychological outcomes which include self-efficacy, QoL, and anxiety and depression; and lastly healthcare usage.

The dietary outcome will be measured using a 15-item Food Frequency Questionnaire (short 15-item FFQ), which has been tested in female patients and widely used in cardiac patients to screen poor dietary patterns and has an overall good agreement with the diet history [63,64].The International Physical Activity Questionnaire-Short Form (IPAQ-SF) is a nine-item self-report tool and is a well-validated tool tested in Australian adults which will be used to assess physical activity, which has good reliability and validity when used in BCS [65,66].The smoking status will be assessed using a self-reported questionnaire.Psychological outcomes include self-efficacy, which will be measured using the General Self-Efficacy Scale (GSES) [67]. The GSES is a 10-item psychometric instrument to measure the participants’ ability to cope with various challenging situations, has good reliability and validity across a range of populations and is recommended for use in pilot studies [67].The QoL will be measured using the Functional Assessment of Cancer Therapy-Breast (FACT-B), a 37-item tool targeted for BC patients, which showed satisfactory reliability and validity [68].The anxiety and depression will be measured using a 14-item Hospital Anxiety and Depression Scale (HADS), which has been widely adopted in cancer patients and in primary care settings and noted to have satisfactory psychometric properties [69].The healthcare usage will be measured using an investigator-created logbook by measuring the number of hospital visits or GP visits for cardiovascular conditions during the phone calls.

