#### 2.2.2. Data Analysis of the Pilot Study

Data will be analysed using descriptive and exploratory inferential statistics using SPSS 26.0 with the intention of feasibility assessment and not for formal hypothesis testing [70]. In a single-group pre-post-test study, the characteristics of the sample will be summarised using descriptive statistics such as frequency counts, percentages, means, and standard deviations. The descriptive data analysis can give an overview of the sample’s age, gender, ethnicity, education level, income, breast cancer treatments, and other demographic variables.

The feasibility outcomes of the study such as recruitment, follow-up assessments, and questionnaire/intervention acceptability will be determined using descriptive data [71]. Mean and standard deviation will be used to analyse interval and ratio data, such as the time taken for participant recruitment and the average time and frequency of physical activity [71]. The acceptability of the questionnaires will be determined by calculating the proportion of missing data [71]. The feedback on the intervention is measured by assessing the participants’ satisfaction scores. Any adverse events related to physical activity, such as musculoskeletal aches and pain, dizziness, and falls, will be presented as the absolute number of events and the total percentage.

Secondary clinical and behavioural outcomes will be presented descriptively at each assessment point to evaluate the feasibility outcomes for future randomization [70]. Changes over time will be explored using non-parametric methods, given the small sample size and single-group pre–post design [71,72]. The Friedman test will be conducted for continuous variables to correlate the data at three different time points [73]. Cochran’s Q test will be utilised for categorical variables to assess changes in proportions between the pre-test and post-test assessments [74]. These analyses will be exploratory only and will not be interpreted as formal hypothesis tests. Analyses will be conducted using available data from participants who complete each assessment. The extent and reasons for missing data will be reported. Participant attrition will be monitored throughout the study, and differences between completers and non-completers will be examined to evaluate potential attrition bias. No imputation of missing data is planned due to the small sample size and feasibility focus of this study.

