This study has several limitations. The study will be conducted in a specific context within the Australian primary care setting, which could limit the generalisability of the results to other settings. Although multiple recruitment channels (e.g., GP referral, primary clinics and social media platforms) will be used to recruit participants in this study, the use of convenience sampling may introduce selection bias, and the findings may not represent the experience and perspectives of all individuals within the target population, limiting the transferability of the results to other settings. No formal sample size calculation was undertaken to test the hypothesis regarding acceptable recruitment and retention rates, as progression criteria were not pre-specified. Instead, the study was exploratory in nature and aimed to estimate the feasibility parameters. The findings will be interpreted as preliminary and descriptive rather than hypothesis-driven. Future studies should incorporate predefined progression criteria and associated hypothesis testing to enable more robust evaluation of recruitment and retention outcomes. This study uses a single-group pre-post-test with a small sample size; hence, the study cannot determine the efficacy of the self-management interventions. Next, the eight-week post-intervention follow-up might be short in duration; however, the primary aim of the study is to assess the feasibility of the intervention and data collection procedures before conducting a future RCT with a longer follow-up. Additionally, it would be challenging to achieve enduring behaviour change among BCSs even though an eight-week follow-up will be conducted as self-management lifestyle interventions require ongoing commitments and lifestyle modifications that may be challenging to maintain. To enhance adherence beyond the scheduled intervention period, future studies can consider including self-monitoring tools, digital reminders, and peer-support mechanisms. Additionally, strategies such as promoting habit formation by linking the desired behaviour to existing daily routines, enhancing intrinsic motivation by placing focus on personal goals, and values rather than external rewards.

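### The primary recruitment rate is calculated only among women who have already come forward and must be willing to be eligible, so it cannot measure uptake; separately, recruitment time is one duration but is assigned a mean and SD.

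*Protocol article*

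**What the plan says.** All references are to the protocol article.

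- **Recruitment rate** (2.2.1, Primary outcomes): "The recruitment rate is the percentage of eligible participants who consented to participate in the study". The same section treats recruitment, retention and dropout as the central aim of the pilot.
- **Route into the study** (2.2, Study procedure): women hear of the study from their doctor, from the centre, or by flyer or reception email. Then "The interested participants will contact the primary researcher". Screening and consent follow: "Prior to recruitment, potential participants will be screened for eligibility, and informed consent will be obtained from eligible participants".
- **Eligibility** (2.2, Study sample): inclusion criterion (6) requires a woman to be "willing to participate in the research study and provide informed consent".
- **Recruitment time** (2.2.1): feasibility of recruitment is "the number of weeks or months needed to achieve the target number of sample size".
- **Its analysis** (2.2.2): "Mean and standard deviation will be used to analyse interval and ratio data, such as the time taken for participant recruitment".
- **Target** (2.2, Sample size): 12 participants, raised to 15 for 20% dropout.

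**The concern.** A recruitment rate from a pilot should tell the planners of the next trial how many women must be offered the study to enrol a given number. Here the denominator forms late. A woman who reads the email and does not reply is never screened, so she is never counted as eligible. A woman who replies and then declines fails criterion (6) as written, so she is not eligible either. Both kinds of non-participation drop out of the calculation, and these are what a recruitment rate is meant to capture.

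The Discussion says the study aims to estimate feasibility parameters ahead of a future RCT and that no progression criteria were set. The descriptive figures are therefore the main quantitative product of the pilot, and one that is near 100% by definition would mislead a reader who took it as uptake.

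The recruitment-time point is smaller. The outcome section defines one number for the whole study, and the analysis section summarises it as though there were a sample of such numbers.

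**Working it through.** **1. The plan's own figure.** 12 / (1 − 0.20) = 15. This reproduces the stated target and is not in dispute. The article states no expected recruitment rate or duration to reproduce.

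**2. The rate with criterion (6) applied literally.** Eligible requires willing and consenting, so numerator and denominator are the same women: 15/15 = 100%. The result would be 100% for any number enrolled.

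**3. The rate with criterion (6) set aside.** Let *c* be the proportion of eligible women informed who contact the researcher, and *k* the proportion of those who consent. Both are assumptions, because the article gives neither.

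- Rate as defined = *k*
- Uptake among eligible women informed = *c* × *k*
- Eligible women informed to obtain 15 consents = 15 / (*c* × *k*)
- Reported rate divided by uptake = 1/*c*

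| *c* (assumed) | *k* (assumed) | Rate as defined | Eligible women informed | Uptake | Ratio 1/*c* |
|---|---|---|---|---|---|
| 10% | 80% | 80% | 188 | 8% | 10 |
| 10% | 100% | 100% | 150 | 10% | 10 |
| 20% | 90% | 90% | 83 | 18% | 5 |
| 50% | 80% | 80% | 38 | 40% | 2 |
| 50% | 100% | 100% | 30 | 50% | 2 |

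The defined rate does not involve *c* at all. The same 15 enrolments are compatible with informing about 30 or about 188 eligible women, and the reported figure would not distinguish between them.

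**4. Recruitment time.** The outcome section yields one observation. Its mean is the value itself. Its sample SD divides by n − 1 = 0 and does not exist. If the analysis section instead means a time for each participant, that could have a mean and SD, but the outcome section does not define it.

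**5. What could be estimated instead.** An accrual rate has a usable interval, but the interval depends on how recruitment ends.

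- Recruitment stops at the 15th participant, so time is the random quantity. Gamma-based 95% limits on the count scale are χ²(0.025; 30)/2 = 8.4 and χ²(0.975; 30)/2 = 23.5.
- The recruitment period is fixed, so the count is random. Exact Poisson limits for 15 are 8.4 and χ²(0.975; 32)/2 = 24.7.

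Dividing by the observed time gives the rate. With an assumed 26 weeks, the estimate is 15/26 = 0.58 per week. The limits are 0.32 to 0.90 if stopped at 15 (8.4/26 and 23.5/26), or 0.32 to 0.95 if the period is fixed (24.7/26).

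**The case against.** The strongest reply has four parts.

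**The denominator is not fixed as narrowly as this.** The study procedure opens by saying that potential participants are identified and approached with the centres, and section 2.2.3 says recruitment activities will be documented and reported at biweekly meetings. An upstream count could therefore exist, and a condensed article may leave flow counts to the full protocol. This stands as far as it goes: the counts could be had cheaply. But the outcome as defined uses none of them, and the procedure places screening after self-referral. The issue is a stated definition that gives the wrong quantity, not an omitted detail.

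**Consent among eligible women is a legitimate measure.** It is, under its proper name and with willingness removed from eligibility. That is why it is relabelled below and not deleted.

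**Time to target guards against a flattering rate.** This also stands. A reader might infer that both recruitment outcomes misstate recruitability, or that the pilot must look feasible by construction. The documents support neither. Time to target does not depend on the rate's denominator and would lengthen if few women responded, and no progression threshold exists for a high rate to pass. Having no value if the target is missed is common to any time-to-target measure. Only the mean-and-SD summary is inapplicable.

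**Not every channel has a denominator.** Flyers cannot be counted by reader, and emails may reach ineligible women. A reader might also take the Discussion's "multiple recruitment channels (e.g., GP referral, primary clinics and social media platforms) will be used to recruit participants in this study" to mean that the pilot recruits through social media. The pilot procedure does not list that channel; it is named for the Phase I interviews. Any uptake rate should therefore be confined to channels that can be counted.

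**Conclusion.** The concern holds for the recruitment rate. As defined, it is 100% under a literal reading of criterion (6). Otherwise it is a conversion rate among volunteers that exceeds uptake by a factor of 1/*c*, which is 2 to 10 if 10–50% of eligible women informed make contact. With 80–100% of those consenting, the plan would report 80–100% against an uptake of about 8–50%. These ranges are assumptions used for scale. The direction of the error and the absence of *c* from the defined rate do not depend on them.

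For recruitment time the conclusion is narrower: the duration is sound, and sections 2.2.1 and 2.2.2 need to be reconciled on how it is summarised. The documents do not say how either figure will be used to size the later RCT, so no particular planning error can be claimed.

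**What to change.** 1. For the denominator only, define eligibility by the clinical and practical criteria and leave out criterion (6). It can remain a condition of enrolment.
2. Relabel the present figure *consent among eligible responders*.
3. Have each centre log the emails and information sheets it issues. Report the counts informed, responding, screened, eligible and consented.
4. Report consented divided by informed as the uptake rate for countable channels, noting that some of those informed may be ineligible. Show flyers and any open channel separately, as counts without a denominator.
5. Report time to target as a single duration and remove it from the mean-and-SD sentence in 2.2.2. If a per-participant time is meant, define it in 2.2.1.
6. Add participants recruited per centre-month, which stays defined if 15 is not reached. Use a gamma-based exact interval if recruitment stops at 15, and a Poisson interval if the period is fixed.

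The cost is a simple tally sheet at each centre, some rewording and a less favourable headline rate. The log should start with the first invitation, since the number of women informed may not be recoverable later.

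### The primary safety outcome is limited to intervention-related effects at the point of collection, with no all-cause event record and no described T1 reference for the named symptoms

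*Protocol article*

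**What the plan says.** Section 2.2.1 states: "The primary outcomes will be the feasibility, acceptability and safety outcomes". Its safety item says that safety includes "discomfort or adverse effects related to NGPS intervention by keeping a daily logbook and reporting via telephone or face-to-face". The item does not name who keeps the logbook or who decides that an effect is related.

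Section 2.2.2 describes the reporting: "Any adverse events related to physical activity, such as musculoskeletal aches and pain, dizziness, and falls, will be presented as the absolute number of events", together with a percentage. This sentence applies a second condition, relation to physical activity, although the intervention may include other strategies such as diet.

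Section 2.2 describes a single group ("a sample size of 12 will be employed in this pilot single-group pre-post study"; 15 recruited to allow for 20% dropout). Entry requires a confirmed cardiovascular diagnosis, with examples that begin "heart failure, hypertension, coronary artery disease, cerebrovascular accidents" and go on to cardiomyopathy and arrhythmias.

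The other relevant data are in sections 2.2.1 and 2.2.2: medical history, weight, BMI, blood pressure, heart rate, FACT-B and HADS, with secondary outcomes tabulated at each assessment point. Healthcare usage is a secondary outcome that counts hospital and GP visits for cardiovascular conditions, with no condition on cause.

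**The concern.** A safety count can be reclassified after the event only if the event was written down. Once relatedness is a condition of collection, an entry that was never made is beyond later review. The entry criteria make this a practical matter. Breathlessness or palpitations in a woman with heart failure or an arrhythmia can readily be put down to the known disease. Table 1 itself attaches cautions about exertion to atrial fibrillation and hypertrophic cardiomyopathy, so cardiac symptoms are a plausible place for a safety signal.

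The opposite error is also possible. The events listed in section 2.2.2 ("such as musculoskeletal aches and pain, dizziness, and falls") include complaints that may already be present at entry, and Table 2 lists pain among survivors' problems. If nobody asks about them at T1, a longstanding ache can be logged as an intervention effect.

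One of three primary outcomes, and the one meant to show whether the programme is safe enough to take forward, would then depend partly on how events happened to be labelled on entry.

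**Working it through.** **1. The plan's own figure.** The number recruited reproduces: 12 / (1 − 0.20) = 15. Nothing in this point changes it.

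**2. What each route captures.**

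| Route (section) | Condition on cause | Safety outcome? | T1 reference described? |
|---|---|---|---|
| Logbook and telephone or face-to-face reports (2.2.1) | Related to the intervention | Yes, primary | No |
| Events presented (2.2.2) | Related to physical activity | Yes | No, for aches, dizziness or falls |
| Cardiovascular GP and hospital visits (2.2.1) | None | No, secondary healthcare usage | Not stated |
| Blood pressure, heart rate, FACT-B, HADS (2.2.1, 2.2.2) | None | No, secondary | Yes |
| Nurse contacts in weeks 1–4 (Table 3) | None | No, care delivery | Not applicable |

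The two routes labelled as safety both carry a relatedness condition. The routes without one are not safety outcomes. A cardiac symptom that leads to no visit, and that the person making the entry does not link to the intervention, has no stated place in the safety data.

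**3. What one misplaced participant does.** At n = 15, one participant is 1/15 = 6.7 percentage points. At n = 12 it is 1/12 = 8.3 points. If no events are recorded, the one-sided 95% upper bound is 1 − 0.05^(1/n), which is 18.1% for n = 15 and 22.1% for n = 12. That bound has its usual meaning only if every event had the chance to be recorded.

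**4. Illustration of the labelling effect (all rates assumed).** Let p be the share of participants with a background ache, dizziness or fall during follow-up, and s the share of those labelled as related. With no true harm, the expected number of participants recorded is 15 × p × s.

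| p | s = 0 | s = 25% | s = 50% | s = 100% |
|---|---|---|---|---|
| 10% | 0 | 0.4 | 0.75 | 1.5 |
| 30% | 0 | 1.1 | 2.25 | 4.5 |
| 50% | 0 | 1.9 | 3.75 | 7.5 |

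For example, 15 × 0.30 × 0.50 = 2.25. At any given p, the result moves only with s, for which the article gives no rule.

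**5. Under-recording.** If only a share a of truly caused cardiac symptoms is recognised as related, 1 − a is lost. The documents give nothing from which to estimate a, so any figure would merely restate the assumption, and I give none.

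**The case against.** The best defence has four parts.

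- **The article condenses a fuller protocol.** Section 2.2.3 promises standard operating procedures for all study procedures. Who judges causality, and how events are graded, may well be set out there, and their absence from the article is not a fault. This stands. It does not reach the stated definition, because a later adjudicator cannot assess an event that the collection rule kept out.
- **The wording leaves room.** The safety item says what safety includes, and relatedness could be read as describing the reported outcome and not a filter on entries. That is possible, but no broader safety collection is stated anywhere in the article.
- **There are other ways to catch events.** A cardiac event that led to a GP or hospital visit would be counted as healthcare usage whatever the participant believed, and Table 3 includes a medical evaluation in week 3. This stands as a partial backstop. It is outside the safety outcome and misses symptoms that prompt no visit.
- **The study is descriptive.** Even a perfect log could not attribute harm in a single group. This is correct, and it limits what the fix can promise. A descriptive count still needs a defined numerator.

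A reader might also infer three stronger things that the article does not support. The first is that participants keep the log and judge cause themselves. This is plausible, since nurse contacts are roughly weekly and the log is daily, but it is not stated. The second is that no health state is recorded at T1. In fact FACT-B, HADS, blood pressure and heart rate are recorded. Their items are not listed, so overlap with the named symptoms cannot be settled here. The third is that most participants would log a false harm. That would require every background symptom to be labelled as related.

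**Conclusion.** The point holds in a limited form. As worded, the primary safety outcome collects related effects only, no all-cause event record is stated, and aches, dizziness and falls have no described T1 reference. In an uncontrolled pilot of 15 women with established cardiovascular disease, the count may be too low for cardiac events and too high for everyday complaints.

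The size of either error is unknown. The table above shows only that the count depends on labelling, and its rates are assumptions. The conclusion rests on reading relatedness as a condition of collection, which is the natural reading of the safety item. It would fall away if the full protocol already requires all events to be logged.

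It would be wrong to conclude that errors could never be detected, because the cardiovascular visit count allows a partial check. It would be equally wrong to expect the change below to separate harm from background illness: without a comparator, it cannot. The change is worth making before data collection because it is cheap and concerns a primary outcome.

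**What to change.** Reword the safety item in section 2.2.1, and the matching sentence in section 2.2.2, as follows:

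1. The logbook and the scheduled contacts record every new or worsened symptom, injury or medical event, regardless of cause.
2. The same named symptoms are noted at T1, and only what is new or worse than T1 counts as an event.
3. Relatedness is assigned afterwards by existing study staff, not at entry.
4. All-cause and related counts are reported side by side, so that section 2.2.2 no longer confines reporting to events linked to physical activity.
5. The cardiovascular GP and hospital visit data are used as a cross-check on the log.

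The cost is revised logbook wording, a short symptom check at T1 and a brief attribution note per event. There will be more entries to review and a higher all-event count, which the report should explain. No extra visits and no change to the sample size are needed.
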